### Interim analyses {21b}

We will conduct one interim analysis when 50% of participants are randomized to evaluate intervention safety and futility. Results of the interim analyses will be made available to the investigators, SO, and NIA PO. Trial termination will only be considered in the following instances: (1) the trial is unable to recruit caregiver participants, (2) the investigators discover a change in average depression in the intervention group that (a) worsens following intervention and (b) worsens to a degree that is greater than any negative changes in the control group for this outcome, and/or (3) we discover reports of unexpected serious adverse events linked to participation in the *Learning Skills Together* intervention in more than 15% of caregivers.

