#### Composition of the data monitoring committee, its role, and reporting structure {21a}

Due to the low-risk nature of this trial, it was determined that a Data Safety Monitoring Board was not required. Instead, a qualified safety officer with relevant clinical and research experiences with family caregivers to persons living with AD/ADRD will review study safety concerns. The SO was approved by the sponsor but remains independent from the sponsor and has no competing interests. The SO will receive a report and meet twice per year with the PI to review study progress, including adverse events and the quality of data collection. The SO will report to the funder.

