### Adverse event reporting and harms {22}

Adverse events are any untoward or unfavorable medical occurrence in a human study participant, including any abnormal symptom or disease, temporally associated with the participant’s involvement in the research, whether or not considered related to participation in the research. The only expected AEs with possibly deleterious outcomes for this study are risks of transient emotional upset experienced during research surveys and/or in processing their caregiving situation during the course of participating in the group-based online course.

Study team members with direct participant contact will complete role-play training to handle cases with risk of harm, such as suicidal ideation. Staff will receive a readily accessible flow chart/decision tree to provide quick guidance. In the case of suspected depression or suicidal ideation where the immediate risk of harm to self or others is not suspected, the study team will provide contact information for the 9–8-8 Suicide Crises Hotline and the Alzheimer’s Association 24/7 Helpline. If a participant affirms suicidal ideation on the PHQ-9 or has a PHQ-9 score of 15 or above, calculated automatically in REDCap survey forms, the threshold for moderately severe depression, we will notify participants of their elevated score and recommend consulting with their healthcare provider. Cases where we suspect elder mistreatment or neglect will be reported to the Adult Protective Services (APS) per Ohio’s mandatory reporting laws. The study team will undergo a learning session on APS referral during training before interacting with participants. When emergency scenarios arise, their handling will be discussed with the investigator team and SO to ensure compliance with emergency procedures. We will work with the SO and the participant on a case-by-case basis to determine whether the participant should be removed from the study due to severe depression or suicidal ideation.

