Any unanticipated serious adverse event (SAE; e.g., death) related to the intervention will be reported to the NIA Program Officer, IRB, and the SO within 48 h of the study team’s knowledge of the SAE. Again, we do not anticipate any SAEs, as this is a low-risk study. Any unanticipated problem (e.g., a lapse in adherence to study procedures) involving risks to study participants or others that are related or possibly related to study participation will be reported to the NIA Program Officer within 48 h of the study team’s knowledge of the event. Self-monitoring, SO reports, and interim analyses, described in other sections, will help the study team to identify unanticipated problems that may occur. The study will provide the NIA Program Officer and the Safety Officer with quarterly reports of any SAE occurring during the study. All related or possibly related SAEs will be reported to the responsible IRB, as well as to the NIA Program Officer and the study’s SO at least annually.

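### Read literally, the closed termination rule keeps unexpected LST-linked SAEs at or below 15% (up to 7 of about 50 LST caregivers, or one related death) from opening the question of stopping

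*Protocol article*

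**What the plan says.** Interim analyses {21b} plans one look, for safety and futility, when half the participants are randomised. It continues: "Trial termination will only be considered in the following instances". The three instances are:

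1. "the trial is unable to recruit caregiver participants".
2. Average depression in the intervention group worsens, and by more than any worsening in the control group.
3. Reports of "unexpected serious adverse events linked to participation in the *Learning Skills Together* intervention in more than 15% of caregivers".

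Other sections bear on the same events:

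- **Adverse event reporting and harms {22}:** "Any unanticipated serious adverse event (SAE; e.g., death) related to the intervention will be reported" to the NIA Program Officer, the IRB and the SO within 48 hours. The section adds: "Again, we do not anticipate any SAEs, as this is a low-risk study". It also says: "Self-monitoring, SO reports, and interim analyses, described in other sections, will help the study team to identify unanticipated problems that may occur". A case-by-case decision is provided to "determine whether the participant should be removed from the study due to severe depression or suicidal ideation".
- **Composition of the data monitoring committee {21a}:** there is no monitoring board. An independent SO reviews safety concerns and meets the PI twice a year. "The SO will report to the funder".

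**The concern.** The word *only* closes the list. Because the sentence governs when termination is considered, it limits even raising the question, not just the decision. The SAE ground is set at a proportion far above what the protocol expects, which is none.

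The grounds are also uneven. The depression ground has no minimum size, so any mean worsening that exceeds the control arm's opens the question. A death related to the intervention does not. It is unlikely that this ordering was intended.

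The stake is participant safety. A related unexpected SAE reaches the right people within 48 hours, but the rule as written then gives them no trial-level step to take on it unless more than 15% of caregivers are affected. The gap concerns SAEs only, since worsening depression already has a low trigger.

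**Working it through.** **Inputs**

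- Total 200, allocation 1:1 (Trial design {8}; Sample size {14}).
- Interim at 50% randomised (Interim analyses {21b}): 0.5 × 200 = 100 caregivers, about 50 in the LST arm.
- Threshold: strictly more than 15% of caregivers (same section). The denominator is not defined. The LST arm is the natural reading, because the events must be linked to LST.
- The protocol gives no event count for the threshold, so there is no stated figure to reproduce, and it gives no SAE rate.

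**Step 1. Smallest count that meets the rule**

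The smallest integer strictly above 0.15 × n is k = floor(0.15 × n) + 1.

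| Denominator n | 0.15 × n | Largest count not meeting the rule | First count meeting it |
|---|---|---|---|
| 30 LST (assumed, fewer counted at the look) | 4.5 | 4 (13.3%) | 5 (16.7%) |
| 40 LST (assumed) | 6.0 | 6 (15.0%) | 7 (17.5%) |
| 50 LST (interim) | 7.5 | 7 (14.0%) | 8 (16.0%) |
| 100 (both arms at the interim, or the full LST arm) | 15.0 | 15 (15.0%) | 16 (16.0%) |
| 200 (all caregivers) | 30.0 | 30 (15.0%) | 31 (15.5%) |

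At n = 50, one related death is 1/50 = 2%. If the denominator is both arms, the rule tolerates more events, so the LST-arm reading is the stricter version of the rule.

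**Step 2. What 7 of 50 would mean**

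The exact (Clopper-Pearson) 95% interval for 7/50 is 5.8% to 26.7%. A count that does not meet the rule is therefore compatible with a true rate well above 15%.

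**Step 3. How often SAEs would occur without meeting the rule**

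Let X be the number of LST caregivers with a linked unexpected SAE, X ~ Binomial(50, p). The rates p are assumptions, and caregivers are taken as independent with a common rate.

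| Assumed p | P(1 ≤ X ≤ 7) | P(3 ≤ X ≤ 7) | P(X ≥ 8) | P(X ≤ 7 given X ≥ 1) |
|---|---|---|---|---|
| 1% | 0.395 | 0.014 | <0.0001 | >0.999 |
| 2% | 0.636 | 0.078 | <0.0001 | >0.999 |
| 5% | 0.920 | 0.456 | 0.003 | 0.997 |
| 10% | 0.873 | 0.766 | 0.122 | 0.877 |

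As a check on the 5% row: P(X = 0) = 0.95^50 = 0.077, and 1 − 0.077 − 0.003 = 0.920.

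Given at least one such event, the rule stays unmet in over 99% of cases at rates of 1% to 5%, and in 88% at 10%.

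**Step 4. Whether another section supplies a route**

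- The 48-hour rule in {22} is notification and attaches no trial-level action.
- The SO's role in {21a} is to review and to report to the funder. No power to recommend a pause or stop is stated.
- The case-by-case decision in {22} concerns one participant's continuation, not the trial's.
- Grounds (1) and (2) in {21b} rest on recruitment and mean depression, so a cluster of SAEs need not trigger either.

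**The case against.** The strongest objection is scope. The sentence sits under the interim heading, straight after the description of that look, and may list only what can lead to stopping there. A related death at another time would then fall outside it. Recruitment failure can be read as part of the look's futility purpose. This reading is possible, and the text does not settle it. It is not the only reading, because failure to recruit is not an interim outcome result and could arise before half are randomised. Nor does it remove the problem: at the one planned safety look, up to 7 linked unexpected SAEs among about 50 LST caregivers would still not open the question.

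Second, the list may bind only the study team. Nothing says it limits the IRB, the funder or the SO, and all of them hear of a related SAE within 48 hours. That is fair as a point about practical risk. But if those bodies can stop the trial, *only* misdescribes the position and the sentence still needs correcting.

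Third, the SO's powers may be set out in a fuller protocol that a journal article condenses. The silence on SO powers would not be a finding by itself. The finding is the explicit, exclusive, numerical rule that the article does state.

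Fourth, the assumed rates have no anchor in the document, and 5% or 10% would be high for a programme in which no SAEs are anticipated. This stands: the probabilities illustrate the rule and do not forecast events. The counts in Step 1 do not depend on them.

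**Conclusion.** The concern holds as a minor wording fault with a safety consequence. Followed literally, and with the recruitment and depression grounds unmet, the rule excludes consideration of stopping for 1 to 7 linked unexpected SAEs among about 50 LST caregivers (2% to 14%), including a single related death.

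This rests on three things: the closed wording, the LST arm at the interim as denominator, and the absence of any other stated trial-level stopping route. Practical risk is low, because SAEs are not expected and reporting continues whatever the rule says. Whether the list is trial-wide or confined to the interim look remains unclear.

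**What to change.** In Interim analyses {21b}:

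1. Strike *only*, so that the three instances oblige consideration of termination without excluding other grounds. Keep the 15% figure as a mandatory trigger.
2. Add: *Independently of these criteria and of the interim analysis, the SO may recommend to the funder that the trial be paused or stopped after reviewing any related unexpected SAE.*
3. As a minor clarification, express the threshold as more than 15% of LST participants.

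The route is an IRB amendment before implementation, as {25} already requires. No added data, visits or staff are needed. The second edit goes beyond wording, since it gives the SO a stated role in pausing or stopping, so the SO and funder should agree to it. The trade-off is slightly less reliance on a fixed count and slightly more on judgement.

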### Methods for additional analyses, including by subgroup {20b}

#### Alternative theory testing with resourcefulness

In addition to primary analyses, the investigators will test resourcefulness as an alternative theory of intervention to explain hypothesized changes in depressive symptomology and negative appraisal of BPSD [32]. If mediation effects for resourcefulness are equal to or greater than those observed for self-efficacy, it will support the application of resourcefulness as an alternative or complementary mechanism of change.

#### Quality of care as an ancillary secondary outcome

Although the intervention is primarily focused on caregiver outcomes to support the delivery of complex care while supporting mental health, it is conceivable that participating in *Learning Skills Together* could affect care delivery. As such, quality of care, measured by the Task Management Strategy Index will be examined in the same manner as secondary outcomes [44].

#### Intervention dosage

Lastly, the investigators will conduct secondary analyses with a subsample of participants who participated in at least four of the six sessions for the assigned study arm. If a high level of non-adherence to the intervention is observed, it may weaken observed intervention effects due to limited intervention exposure. In this case, secondary analyses could help disentangle intervention efficacy from potential feasibility issues. Though failure to observe intervention effects in primary analyses would still indicate a lack of efficacy, secondary analyses could help inform the next steps in modifying and testing *Learning Skills Together*.

### Methods in analysis to handle protocol non-adherence and any statistical methods to handle missing data {20c}

Non-complete cases, due to situations such as changes in eligibility between survey waves (e.g., care recipient deceased) and skipped surveys, will be treated using an intent-to-treat analysis. This means that all data from participants who completed a baseline survey and were randomized will be analyzed as members of the group into which they were randomized. We will conduct bivariate comparisons between study completers and non-completers to determine factors associated with dropping out, including group assignment. Missing data at the construct level will be handled using multiple imputations using chained equations (MICE). Imputed data sets will be used to fit the GEE models. Covariates that demonstrate a bivariate association with missingness will be included as auxiliary variables to inform imputations. The results with imputation will be summarized using Rubin’s rules and compared with the GEE models using complete cases.

### Plans to give access to the full protocol, participant level-data, and statistical code {31c}

De-identified research data will be shared at the National Archive of Computerized Data on Aging (NACDA), an NIH-funded repository. Documentation, such as code names and original survey questions, and protocol documents, will also be uploaded to the repository in compliance with NACDA requirements (e.g., code names usable across software packages). We will also document meta-data (e.g., study title, investigator team). Data will be accessible to investigators working under an institution with a Federal Wide Assurance (FWA) and could be used for secondary study purposes. Sharing of analytic code will be provided at the discretion of the investigator team, based on the assessed qualification of the access requester, where “expert users” with an advanced academic degree or other relevant experience will be provided with code files. De-identified data will be made available as soon as possible but no later than within 1 year of the completion of the funded project period for the parent award or upon acceptance of the data for publication, or public disclosure of a submitted patent application, whichever is earlier.

## Oversight and monitoring

### Composition of the coordinating center and trial steering committee {5d}

The PI and project manager are at the core of the study coordinating center. They are responsible for hiring and coordinating staff, including undergraduate, graduate, and professional research assistants and associates, who will conduct routine activities such as data collection and day-to-day recruitment activities. This team will meet once per week, either in-person or remotely. The project manager will also coordinate nurse interventionists who will deliver the intervention and who are hired on a contract basis. Nurse interventionists will meet with the PI or project manager at least quarterly to identify challenges and coordinate coverage for upcoming sessions. The investigator team, responsible for monitoring study progress and providing input on how to respond to challenges, will meet monthly.

#### Composition of the data monitoring committee, its role, and reporting structure {21a}

Due to the low-risk nature of this trial, it was determined that a Data Safety Monitoring Board was not required. Instead, a qualified safety officer with relevant clinical and research experiences with family caregivers to persons living with AD/ADRD will review study safety concerns. The SO was approved by the sponsor but remains independent from the sponsor and has no competing interests. The SO will receive a report and meet twice per year with the PI to review study progress, including adverse events and the quality of data collection. The SO will report to the funder.

### Adverse event reporting and harms {22}

Adverse events are any untoward or unfavorable medical occurrence in a human study participant, including any abnormal symptom or disease, temporally associated with the participant’s involvement in the research, whether or not considered related to participation in the research. The only expected AEs with possibly deleterious outcomes for this study are risks of transient emotional upset experienced during research surveys and/or in processing their caregiving situation during the course of participating in the group-based online course.

Study team members with direct participant contact will complete role-play training to handle cases with risk of harm, such as suicidal ideation. Staff will receive a readily accessible flow chart/decision tree to provide quick guidance. In the case of suspected depression or suicidal ideation where the immediate risk of harm to self or others is not suspected, the study team will provide contact information for the 9–8-8 Suicide Crises Hotline and the Alzheimer’s Association 24/7 Helpline. If a participant affirms suicidal ideation on the PHQ-9 or has a PHQ-9 score of 15 or above, calculated automatically in REDCap survey forms, the threshold for moderately severe depression, we will notify participants of their elevated score and recommend consulting with their healthcare provider. Cases where we suspect elder mistreatment or neglect will be reported to the Adult Protective Services (APS) per Ohio’s mandatory reporting laws. The study team will undergo a learning session on APS referral during training before interacting with participants. When emergency scenarios arise, their handling will be discussed with the investigator team and SO to ensure compliance with emergency procedures. We will work with the SO and the participant on a case-by-case basis to determine whether the participant should be removed from the study due to severe depression or suicidal ideation.

Any unanticipated serious adverse event (SAE; e.g., death) related to the intervention will be reported to the NIA Program Officer, IRB, and the SO within 48 h of the study team’s knowledge of the SAE. Again, we do not anticipate any SAEs, as this is a low-risk study. Any unanticipated problem (e.g., a lapse in adherence to study procedures) involving risks to study participants or others that are related or possibly related to study participation will be reported to the NIA Program Officer within 48 h of the study team’s knowledge of the event. Self-monitoring, SO reports, and interim analyses, described in other sections, will help the study team to identify unanticipated problems that may occur. The study will provide the NIA Program Officer and the Safety Officer with quarterly reports of any SAE occurring during the study. All related or possibly related SAEs will be reported to the responsible IRB, as well as to the NIA Program Officer and the study’s SO at least annually.

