### Criteria for discontinuing or modifying allocated interventions {11b}

Participants may choose to withdraw from the study at any time. Participants may withdraw already collected research data so long as data are not yet de-identified. Participants may also be withdrawn if they become ineligible to participate, such as if the person they care for passes away. Involuntary withdrawal may occur if it is suspected that an individual is impersonating a caregiver or if their participation in the intervention or control group programs is considered overly disruptive to other participants. If this occurs, the participant will be notified by email. We will retain study data collected to that point unless otherwise requested.

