### Participant timeline {13}

Participants will complete a baseline survey up to 3 weeks before randomization. Once randomized, they will participate in either the intervention or control group condition once weekly for 6 weeks. A follow-up survey will be completed within 3 weeks post-intervention. A third and fourth follow-up survey will be administered 3 and 6 months post-intervention. Once the participant completes all study activities, they will receive the workbook materials for whichever program into which they were not randomly allocated to participate. Figure 1 illustrates this timeline.

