#### Self-efficacy as a mediator of intervention effects

To test self-efficacy as a mediator of secondary outcomes, we will adopt a structural equation modeling approach, which comprises two sequential models. In this analysis, the outcome will be the change score for depression or appraisal of BPSD, which is calculated by the score at 6 months minus the score at baseline. The mediator will be the change score for self-efficacy, tested using the Self-Efficacy Scale-8, calculated by 3 months minus the baseline score. Direct and indirect effects will be estimated using Baron’s and Kenny’s method [54] (Fig. 2).

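### Removal for severe depression is from the study, not only from sessions, so later PHQ-9 and self-efficacy scores can be lost for an outcome-related reason; expected bias is small and the fix is cheap

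*Protocol article*

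**What the plan says.** In Adverse event reporting and harms {22}, affirming suicidal ideation on the PHQ-9, or scoring 15 or more, leads to notification and advice to see a healthcare provider. Separately, the team works with the safety officer and the participant "on a case-by-case basis to determine whether the participant should be removed from the study due to severe depression or suicidal ideation". No PHQ-9 cut-off is attached to that removal. The same section counts among the expected harms "risks of transient emotional upset experienced during research surveys".

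In Criteria for discontinuing or modifying allocated interventions {11b}, the text on involuntary withdrawal ends: "We will retain study data collected to that point unless otherwise requested". The reasons named there are ineligibility, suspected impersonation and disruption. Depression is not among them.

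The Participant timeline {13} places the first outcome survey after the programme: "A follow-up survey will be completed within 3 weeks post-intervention". A caregiver removed during the six weeks would have no PHQ-9 score after baseline.

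The missing-data section {20c} analyses everyone as randomised and imputes by chained equations: "Imputed data sets will be used to fit the GEE models". The results are then "compared with the GEE models using complete cases". Interim analyses {21b} lists among the grounds for stopping that "the investigators discover a change in average depression in the intervention group that (a) worsens following intervention", together with a worsening greater than any in the control group.

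**The concern.** The reason for removal is the extreme of an outcome the trial measures. If removal ends the surveys, the trial stops observing the caregivers who matter most for judging harm, and it also loses their later scores on the primary self-efficacy scale. Analysing people as randomised and imputing gaps governs the analysis. It does not keep data collection going.

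The arms could differ in removals for two reasons. One programme may worsen or relieve depression more than the other. Also, the study team shares in the decision, and the PI and project manager are unblinded (Who will be blinded {17a}). Removing depressed caregivers mainly from the LST arm makes LST look better on PHQ-9; removing them mainly from control makes control look better.

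**Working it through.** **The plan's own figure.** The article gives no number for removals. Its sample size does reproduce. With d = 0.54, 80% power and α = 0.05 (two-sided assumed), the normal formula gives n = 2(1.960 + 0.842)²/0.54² = 53.8, or 54 per arm. The exact t-test needs 55 per arm (power 80.1%), so N = 110. The allowance from 200 to 110 is 90/200 = 45% attrition, so the fix does not change N.

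**What the sections say together.** Section {22} removes from the study. Section {11b} distinguishes leaving the study from taking part in the programmes, and keeps only data already collected. Section {20c} handles gaps in the analysis. None of the three offers surveys after removal.

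**Size of the bias.** The documents give no PHQ-9 distribution or removal rate, so all inputs here are assumptions:
- PHQ-9 at four surveys, mean 8, SD 5.5, rounded and limited to 0–27.
- Correlation AR(1) 0.75; exchangeable 0.6 as a variant.
- Removal at PHQ-9 of 20 or more, or 15 or more, with probability 0.25, 0.5 or 1. The 15 is the notification threshold, used as a stand-in because no cut-off for removal is stated.
- Recorded trigger: the score at the post-intervention or 3-month survey. Unrecorded trigger: the 6-month state itself, which is the hardest case for imputation.
- In both cases the 6-month score is lost. Imputation is an arm-specific regression on the three earlier scores, standing in for chained equations.
- 400,000 simulated caregivers per arm.

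The quantity compared is the LST-minus-control difference in mean change from baseline to 6 months. Bias is the estimate with removed caregivers lost minus the estimate with everyone surveyed. Absolute values in PHQ-9 points, AR(1) 0.75 unless stated:

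| Trigger and pattern | Removed | Complete cases | After imputation |
|---|---|---|---|
| Recorded, same rule in both arms, effect 0, −1.5, −2 or +2 (both correlations) | varies | 0.00–0.02 | 0.00–0.01 |
| Recorded, one arm only, no effect | 0.7–17% of that arm | 0.00 | 0.00 |
| Unrecorded, same rule, no effect | 0.5–12% of each arm | 0.00–0.01 | 0.00–0.01 |
| Unrecorded, 20 or more, one arm only, no effect | 0.5–1.8% of that arm | 0.04–0.15 | 0.03–0.12 |
| Unrecorded, 15 or more, probability 0.25–0.5, one arm only, no effect | 3–6% of that arm | 0.16–0.33 | 0.13–0.28 |
| Unrecorded, 15 or more, all removed, one arm only, no effect | 12% of that arm | about 0.7 | about 0.7 |

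Two checks on these rows:
- With exchangeable correlation 0.6, the two one-arm rows with partial removal or a cut-off of 20 give 0.03–0.13 and 0.15–0.32 after imputation.
- A common rule with an unrecorded trigger and a true effect of −1.5, −2 or +2 also removes unequal numbers. The bias after imputation is then 0.01 to 0.17 toward the null (probability 0.25–0.5, both correlations).

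**Scale.** Under AR(1) 0.75 the baseline-to-6-month correlation is 0.75³ = 0.42. The SD of change is 5.5 × √(2 × 0.58) = 5.9, and the standard error with 55 per arm is 5.9 × √(2/55) = 1.13. A bias of 0.28 is about a quarter of that.

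**The case against.** The strongest reply has four parts.

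First, the planned analysis uses imputed data, and where a recorded score triggers removal the bias is negligible. This stands, and it is why the point is small.

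Second, the clause is a discretionary safety decision with no threshold, and what happens to surveys afterwards may be operational detail in the full protocol. That the clause is discretionary stands. But the article does state the action, and the action is removal from the study. If the full protocol already continues surveys, the article's wording should say so.

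Third, nothing indicates that removals would fall in one arm. This also stands; the one-arm rows show what could happen and are not a forecast.

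Fourth, the safety officer takes part in these decisions and receives interim results, and completers are to be compared with non-completers by group. So individual safety oversight is not in question. That comparison describes the loss but does not recover the scores.

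A reader might infer more than the documents support:
- **That everyone scoring 15 or more is removed**, giving the 0.7-point row. That score leads only to notification and advice.
- **That the final comparison shifts by several tenths of a point among completers.** This applies to raw 6-month means. The plan works with change from baseline (Outcomes {12}), where the recorded-trigger bias is 0.00 to 0.02.
- **That a few removals would swing the interim rule.** This needs removed caregivers to have worsened by far more than a model of this kind gives, which is a mean change of about 0 to 2 points from baseline to post-intervention for those removed mid-programme.
- **That the mediation analysis ignores imputation.** Its depression outcome is a change score, "which is calculated by the score at 6 months minus the score at baseline", but section {20c} states chained-equation imputation generally. Naming the GEE models next does not exclude mediation.

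**Conclusion.** The concern holds in a limited form. The stated action ends study participation for a reason tied to PHQ-9, no section continues surveys, and the lost scores cannot be recovered at analysis.

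The likely effect is about 0.00 to 0.02 PHQ-9 points in 6-month change when a recorded score triggers removal, or when both arms follow one rule and there is no true effect. A range of about 0.03 to 0.28 points after imputation arises with no true effect only if removals follow unrecorded worsening and fall mainly in one arm. A common rule combined with a true effect and an unrecorded trigger stays within the top of that range. The sign depends on the arm.

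These sizes rest on assumed means, SD, correlations and removal probabilities. No size was computed for self-efficacy, which would lose scores from the same people. This does not threaten the trial's primary conclusion. The case for change is that the loss is outcome-related, irreversible and cheap to avoid.

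**What to change.** In Adverse event reporting and harms {22}, make the action discontinuation of the group sessions. State that the remaining surveys, at minimum the PHQ-9 and the 8-item self-efficacy scale, will still be offered unless the participant withdraws consent or the safety officer judges further surveys clinically inappropriate. The exception is needed because the section itself names surveys as a source of upset. It will still lose some scores.

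At the interim analysis, tabulate by arm the number removed or withdrawn before the post-intervention survey, with the reason and the last PHQ-9 score.

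The cost is a wording amendment, a clarification in the consent form and one small table. The surveys are already remote, scheduled and staffed, and the sample size is unchanged. The downside is a few extra survey contacts with caregivers who have left the sessions.
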